**Figure 2 f2:**
[figure not shown]
G*Power-based sample size calculation for a repeated-measures ANOVA with a within-between interaction. The plot depicts an *a priori* power analysis to determine the required sample size for a repeated-measures analysis of variance examining the interaction between a between-subjects factor (2 groups) and a within-subjects factor (6 measurement time points). The upper panel shows the central F-distribution under the null hypothesis (red solid curve) and the noncentral F-distribution under the alternative hypothesis (blue dashed curve). The critical F-value (2.22502) is indicated by the green vertical line. The red shaded region represents the α error probability (Type I error, set at 0.05), and the blue shaded region denotes the β error probability (Type II error), with power (1−β) targeted at 0.95. Input parameters include: effect size (f) = 0.1, α = 0.05, number of groups = 2, number of repeated measurements = 6, correlation among repeated measures = 0.5, and sphericity correction (ϵ) = 1. Output parameters reveal a total required sample size of 166, a noncentrality parameter (λ) of 19.92, numerator degrees of freedom (df) = 5, denominator df = 820, and an actual power of ~0.95.

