### Comparative efficacy of ECT vs. MST

Previous head-to-head studies comparing the antidepressant efficacy of ECT and MST have generally found comparable treatment outcomes (14). However, recent research has provided further insights into the effectiveness of these therapies through controlled clinical trials and systematic reviews. A double-blinded, randomized clinical trial conducted by Deng et al. (15). compared the antidepressant effects of MST, applied at 100 Hz for 10 seconds at 100% of the maximum device power, with ultrabrief pulse right unilateral ECT, applied at 6 times seizure threshold. Both MST and ECT demonstrated clinically meaningful antidepressant effects, with similar response and remission rates observed in both treatment groups. Additionally, an open-label study by Daskalakis et al. (16). evaluated the efficacy of MST at different frequencies (i.e., high-frequency MST at 100 Hz, medium-frequency MST at 60 or 50 Hz, and low-frequency MST at 25 Hz) using 100% stimulator output. Among patients with MDD, high-frequency MST produced the highest remission rate, indicating its potential as an effective treatment option. In a study by Kayser et al. (7), twenty patients with treatment-resistant depression were randomly assigned to receive either MST or ECT. The study found that both treatments produced a statistically significant and similar improvement in depressive symptoms, as measured by a 50% reduction in Montgomery Åsberg Depression Scale ratings. Several systematic reviews have also examined the comparative efficacy of MST versus ECT for depression treatment. Cai et al. (17). summarized four randomized controlled trials (RCTs) and found no significant differences in response, remission, or improvement in depressive symptoms between MST and ECT. Similarly, a meta-analysis by Chen et al. (18). included data from 10 studies comprising a total of 285 patients. The analysis revealed no significant difference in the antidepressant effect between MST and ECT, further supporting the equivalence of these treatments in depression management.

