### Sample size estimation

The sample size calculation for this study was conducted through *a priori* power analysis using G*Power 3.1.9.7 (29). Parameters were chosen, including α = 0.05 and power (1-ß) = 0.95. An effect size of f = 0.1 was selected based on previous research findings (15). Specifically, in the intent-to-treat sample (N = 73), 18 participants (51.4%) in the MST group (N = 35) and 16 (42.1%) in the ECT group (N = 38) met response criteria, while 13 (37.1%) in the MST group and 10 (26.3%) in the ECT group met remission criteria. In addition to the two experimental conditions (MST and ECT), covariates including age, sex, duration of illness, age of onset, intelligence quotient (IQ), and antidepressant usage were considered, resulting in a total of 6 covariates. Accounting for a potential dropout rate of 20%, the final estimated number of participants required for the study was determined to be 210. (**Figure 2**).

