### Intervention

Patients will receive either MST, administered at a frequency of 100 Hz with 100% of the maximum device power for a duration of 10 seconds, or bitemporal ECT, according to routine clinical practice at SMHC following the ECT clinical practice guideline in China. The electrical stimulation wave width will be 0.5 ms. The energy of electrical stimulation will be determined according to the patients’ age(age × 0.8 × 100%) and increased by 5% until a proper seizure (seizure duration of 15 seconds or longer) is achieved.

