Appropriate statistical methods will be employed for data analysis, including mixed-effects models for repeated measures (MMRM). MMRM with a factorial design (3 time points × 2 conditions) will be conducted to examine significant interactions between time (baseline, Day 30, and Week 12) and condition (ECT and MST), while adjusting for potential covariates such as age, sex, duration of illness, age of onset, IQ, and antidepressant usage. This approach is robust to missing data under the missing-at-random (MAR) assumption and provides unbiased estimates of treatment effects. The significance level will be set at 0.05.

Sensitivity analyses will be performed to assess the robustness of results to missing data, including multiple imputation (MI) under MAR and missing-not-at-random (MNAR) assumptions. Results from MMRM and MI will be compared. Exploratory analyses will include subgroup analyses by demographic/clinical characteristics and correlation analyses between neurophysiological biomarkers (EEG/ECG) and treatment outcomes, using linear or logistic regression models as appropriate.

Subgroup analyses will compare relapse rates and time-to-relapse between participants who received maintenance treatments versus those who did not, within both MST and ECT groups. This will help disentangle the effects of acute treatment from post-treatment management strategies.

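### The 95% power behind N = 210 belongs to a six-time-point test for a difference, not to the three-time-point model or the non-inferiority question the protocol states

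*Protocol article*

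**What the plan says.** The Sample size estimation section sets alpha at 0.05 and power at 0.95. It says that "An effect size of f = 0.1 was selected based on previous research findings (15", and supports this with response rates (51.4% on MST, 42.1% on ECT) and remission rates (37.1% and 26.3%) from one earlier trial. After a 20% allowance for dropout, "the final estimated number of participants required for the study was determined to be 210".

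The Figure 2 legend prints the whole run. It is a repeated-measures ANOVA "examining the interaction between a between-subjects factor (2 groups) and a within-subjects factor (6 measurement time points". The inputs are "effect size (f) = 0.1, α = 0.05, number of groups = 2, number of repeated measurements = 6", with "correlation among repeated measures = 0.5, and sphericity correction (ϵ) = 1". The outputs are N = 166, a noncentrality parameter of 19.92, 5 and 820 degrees of freedom, a critical F of 2.22502 and power of about 0.95.

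Other sections describe something else:

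- **Data entry and analyses** plans an "MMRM with a factorial design (3 time points × 2 conditions", the times being baseline, Day 30 and Week 12.
- **Clinical measures** schedules the HDRS-24 eight times: baseline, after sessions 3, 6, 9 and 12, and at weeks 4, 8 and 12 of follow-up.
- **Study summary** schedules EEG and ECG six times. This is the only schedule that matches the six in the power run, and the EEG and ECG analyses are described as exploratory.
- **Study design** calls the trial non-inferiority, and **Primary outcome** names HDRS-24 change from baseline to the 12-week follow-up.

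**The concern.** A stated power is useful only if it belongs to the test that will answer the trial's question. Here it belongs to a different one in two respects.

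First, the number of time points differs from the stated model. In this G*Power procedure the noncentrality parameter is proportional to the number of measurements, so six against three is not a cosmetic difference.

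Second, and more important, the run gives the chance of detecting that two trajectories differ. A non-inferiority claim needs the chance that a confidence limit excludes a margin when the treatments are truly alike. A non-significant interaction does not show non-inferiority, and a significant one could favour either arm.

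The effect size adds a third difficulty. The support offered for f = 0.1 is binary, favours MST, and comes from a trial whose comparator was "ultrabrief pulse right unilateral ECT, applied at 6 times seizure threshold", whereas the comparator here is MST "or bitemporal ECT, according to routine clinical practice at SMHC" in the Intervention section's wording of the two arms. At stake is the only basis given for N: a reader would take the trial to have a 95% chance of answering its own question, and that has not been shown.

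**Working it through.** **Step 1. Reproduce the printed run.** Inputs from the Figure 2 legend: f = 0.1, correlation ρ = 0.5, ε = 1, k = 2 groups, m = 6 measurements, N = 166.

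- λ = f² × N × m / (1 − ρ) = 0.01 × 166 × 6 / 0.5 = 19.92
- df1 = (k − 1)(m − 1) = 5; df2 = (N − k)(m − 1) = 164 × 5 = 820
- critical F = 2.22502; power from the noncentral F = 0.9501

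Every printed figure is reproduced. N = 164 gives 0.947, so 166 is the minimum. Dropout: 166 / 0.8 = 207.5, so 208; 210 fits seven sites of 30. Conversely, 210 × 0.8 = 168 evaluable, or 84 per arm.

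**Step 2. Three time points, with f = 0.1 and ρ = 0.5 kept.** λ = 0.01 × N × 3 / 0.5 and df1 = 2.

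| N analysed | λ | df2 | power |
|---|---|---|---|
| 166 | 9.96 | 328 | 0.810 |
| 168 | 10.08 | 332 | 0.815 |
| 210 | 12.60 | 416 | 0.896 |

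The result is sensitive to ρ: at N = 166 it is 0.66 for ρ = 0.3 and 0.96 for ρ = 0.7.

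**Step 3. Three time points, with the raw difference kept instead.** Interaction f depends on the pattern of group differences over time. Assume no difference at baseline and a constant difference d (in SD units) afterwards. With two equal groups, f is half the standard deviation of the differences across the time points.

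- m = 6: f = d√5 / 12, so f = 0.1 means d = 0.537
- m = 3: f = d√2 / 6, so d = 0.537 means f = 0.1265 (f² = 0.016)
- λ = 0.016 × 166 × 3 / 0.5 = 15.94; power 0.954 at N = 166, and 0.956 at N = 168 (λ = 16.13)

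Keeping f = 0.1 with three points instead means d = 0.1 × 6 / √2 = 0.424. Step 2 therefore targets a smaller raw difference than the six-point run did under this pattern.

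**Step 4. What 168 evaluable would give for non-inferiority (illustration).** The article gives neither a margin nor an SD, so margins are in units of the HDRS-24 SD at one visit. Assume a true difference of zero, one-sided 0.025, ρ = 0.5 and 84 per arm.

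- margin = (1.960 + z for power) × √(2v / 84)
- change score: v = 2(1 − 0.5) = 1; baseline-adjusted: v = 1 − 0.5² = 0.75

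| power | change score | baseline-adjusted |
|---|---|---|
| 95% (z = 1.645) | 0.56 SD | 0.48 SD |
| 80% (z = 0.842) | 0.43 SD | 0.37 SD |

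These are the smallest margins that could be tested at each power. They show what a proper calculation would look like; they are not proposed margins.

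**The case against.** The strongest reply concerns the power loss. A reader might infer that moving from six points to three cuts power from 95% to 81%, raises the type II error from 5% to 19%, or means that 260 should be analysed and 325 enrolled. The protocol does not support any of these as a flat statement. They hold f at 0.1 while the number of time points changes, and under a constant difference after baseline that quietly reduces the target from 0.54 SD to 0.42 SD. With the raw difference held, power stays at about 0.95. They also assume that only 166 to 168 contribute, whereas the protocol plans intention-to-treat analysis, multiple imputation and continued assessment of withdrawn participants, so the effective number lies between 168 and 210. This objection stands, and the 0.81 must be given with its conditions. Holding f is still a fair literal reading, because f is what the protocol states.

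A reader might also call this an arithmetic error. It is not: the printed run is right in every figure.

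Three further replies have some force. The analysis section does not label the three-point model as primary. The binary rates may have been converted: Cohen's h for 51.4% against 42.1% is 0.187, and half of it is 0.093, close to 0.1. But that is a between-group quantity and does not describe an interaction over time. Finally, a margin may exist in a full protocol or SAP not shown here, so its absence from the article is not the complaint. It does not rescue the calculation, which is printed with all its inputs, uses no margin, and is what produced 210.

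**Conclusion.** The point holds as an inconsistency between the powered test, the stated analysis and the stated objective. The 0.95 is correct for a six-point group-by-time difference test. It is not shown for the three-point model, where power is 0.81 to 0.90 (166 to 210 analysed) if f = 0.1 and ρ = 0.5 are kept, and about 0.95 if a constant 0.54 SD difference after baseline is kept. It has no bearing on the non-inferiority comparison, and that conclusion does not depend on any of these assumptions. The response and remission rates cited do not support a within-between f for this trial: they are binary, they favour MST, and the ECT comparator differed. Nothing here shows that 210 is too few. Whether it is enough depends on a margin and SD that the calculation does not use.

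**What to change.** Withdraw the 0.95 power statement and Figure 2 as the justification for the non-inferiority comparison, and keep N = 210. Restate the calculation for the Week-12 HDRS-24 difference: one-sided 0.025, a named margin and SD with their sources, a true difference of zero rather than one favouring MST, and about 168 evaluable. Say whether the analysis uses the change score or adjusts for baseline, and report the power delivered at the chosen margin. If the three-point interaction is kept as a supporting analysis, give its power with the assumed pattern of differences and correlation.

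The cost is one rewritten paragraph and one replaced figure, with no added patients. The drawback is that the stated power may come out below 0.95.

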### Randomization procedure and blinding

A permuted block randomization method will be utilized to allocate participants to treatment groups at each study site. The sample size was consistent across sites, with 50% of participants assigned to receive ECT and the remaining 50% allocated to receive MST. Both clinical staff and participants were blinded to the treatment assignment. Randomization numbers were sealed in opaque envelopes, which were opened by the designated seizure therapy technician responsible for administering either ECT or MST treatment, based on the randomization numbers, only at the start of treatment. Randomization occurred on Day 1 immediately following baseline data collection. Following completion of the intervention, participants will be asked to provide feedback on whether they believe they received ECT or MST stimulation.

### Assessments

#### Clinical measures

Clinical assessments will be administered by blinded raters at various time points throughout the study, including baseline, post-session 3, 6, 9, and 12 (3 hours after each session), as well as at the 4-week, 8-week, and 12-week follow-up visits. The primary outcome measure was the total score on the 24-item Hamilton Depression Rating Scale (HDRS-24) (28). Additionally, the Hamilton Anxiety Scale (HAMA) (30), clinician-rated, served as a secondary outcome measure. Other assessments included self-reported measures such as the Self-Rating Depression Scale (SDS) (31) and the Self-Rating Anxiety Scale (SAS) (32), as well as clinician-rated measures including the Global Assessment of Functioning (GAF) scale (33). Follow-up assessments were conducted monthly. Prior to the commencement of the experiment, all subjects will undergo an interview using the MINI-International Neuropsychiatric Interview (M.I.N.I. 5.0) (34). Additionally, participants filled out a self-administered questionnaire to provide demographic information.

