### Comparative side-effect of ECT vs. MST

The comparison of cognitive side effects between ECT and MST in the treatment of MDD has yielded varying conclusions. However, the majority of studies suggest that MST results in fewer physical side effects and no cognitive impairments compared to ECT. In a RCT by Deng et al. (15), patients receiving ECT reported higher severity of headache, nausea, and muscle pain compared to those receiving MST. Furthermore, patients receiving ECT experienced greater confusion or disorientation, and took significantly longer to regain orientation compared to MST (19). Autobiographical recall is linked to temporal cortices, notably the hippocampus. This suggests that ECT may exert a more detrimental effect on the hippocampus compared to MST. This supports the cognitive safety of MST, as evidenced by negligible cognitive adverse effects and superior performance in autobiographical memory recall. A systematic review (20) focusing on the cognitive effects of MST found little to no adverse cognitive effects. While some RCTs comparing MST and ECT reported inconsistent results regarding cognitive effects, the accumulated evidence indicates that MST has fewer adverse cognitive effects compared to ECT (17). A pilot study by Fitzgerald et al. (21) compared the cognitive effects of 100 Hz MST and ECT in patients with persistent depression. Significant improvements in psychomotor speed, verbal memory, and cognitive inhibition were observed following MST, with no reductions in cognitive performance. Conversely, ECT resulted in significant improvement in only one cognitive inhibition task. Furthermore, the MST group showed significantly greater improvement in psychomotor speed compared to ECT. In an open-label study by Kayser et al. (7), MST was investigated as an add-on therapy to controlled pharmacotherapy for treatment-resistant depression (TRD). No cognitive side effects were observed in either group, suggesting the cognitive safety of MST. Polster et al. (22) aimed to broaden insight into the side effect profile of MST compared to ECT by examining the disruption of acute verbal memory processes after treatment. Overall, evidence from clinical trials and systematic reviews suggests that MST is associated with fewer physical side effects and superior cognitive safety compared to ECT in the treatment of MDD.

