### Study summary

**Figure 1** provides an overview of the study flow. Participants will be randomly allocated to either the ECT or MST group. Each center aims to recruit 15 participants for each group (ECT and MST), using block randomization, resulting in a total of 30 participants per center (15 per group). Across seven centers, this will yield a total sample size of 210 participants (105 per group). The trial comprises a 12-session intervention phase of ECT/MST, spanning approximately 4 weeks, followed by a 12-week observation period. For the first three treatment sessions, participants will receive consecutive sessions. Subsequently, there will be a one-day interval between sessions 4 to 6, a two-day interval between sessions 7 to 9, and a three-day interval between sessions 10 to 12, ensuring completion within a month. Following treatment completion, participants will undergo follow-up clinical observations every four weeks for 12 weeks. EEG and ECG recordings will be obtained at baseline, post-session 3, 6, 9, 12 (3 hours after each session), and at the 12-week follow-up. All evaluations will be conducted under standardized conditions throughout the sessions. **Table 1** delineates the time points for clinical assessments, interventions, and electrophysiological examinations.

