**Figure 1 f1:**
[figure not shown]
Flow diagram of the study design. This flowchart outlines the trial design comparing electroconvulsive therapy (ECT) and magnetic seizure therapy (MST) in patients with major depressive disorder (MDD). A total of 210 MDD participants (recruited from 7 centers, 30 per center) undergo screening and enrollment with informed consent. At baseline (Day 0), demographic/clinical assessments and electrophysiological measurements (EEG/ECG) are conducted. Participants are then randomized via blocked randomization to either the ECT group (n=105) or MST group (n=105). Treatment sessions are delivered in four phases: Days 1–3 (sessions 1–3, daily), Days 4–9 (sessions 4–6, every 2 days), Days 10–18 (sessions 7–9, every 3 days), and Days 19–30 (sessions 10–12, every 4 days). Clinical/cognitive assessments and EEG/ECG measurements are performed after every 3 sessions (end of each phase). A 12-week post-intervention follow-up includes clinical/cognitive assessments every 4 weeks, with additional EEG/ECG measurements at week 12.

**Table 1 T1:** Schematic summary and milestones for enrolment, ECT/MST treatment, and assessments across the study time-line.

Time-point	Eligibility screen	Informed consent	Allocation	Intervention (ECT/MST)	Assessments			
					Demographic features	Clinical /Cognitive performances	EEG	ECG
Day 0	X	X	X		X	X	X	X
Treatment phase								
Day 1				X				
Day 2				X				
Day 3				X		X	X	X
Day 5				X				
Day 7				X				
Day 9				X		X	X	X
Day 12				X				
Day 15				X				
Day 18				X		X	X	X
Day 22				X				
Day 26				X				
Day 30				X		X	X	X
Post-treatment phase								
Week 4						X		
Week 8						X		
Week 12						X	X	X

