#### Cognitive assessments

The assessors conducting cognitive tests will be blinded to the group allocation of the patients. Moreover, the timing of the cognitive assessments will coincide with the time points of clinical evaluations. The WASI will be utilized to evaluate intellectual function. Consisting of four subtests, the WASI assesses two verbal aspects of crystallized intelligence (vocabulary and similarities) and two nonverbal measures of fluid intelligence (block design and matrix reasoning). While the WASI subtests share similarities with those found in the Wechsler Adult Intelligence Scale – Third Edition, they feature distinct items. Cognitive function will be assessed in the study using a battery of eight tests, with the Hopkins Verbal Learning Test-Revised (HVLT-R) designated as the primary cognitive outcome (evaluating verbal learning and memory). The remaining seven tests serve as secondary cognitive outcomes: Trail Making Test Part A (TMT-A), Brief Assessment of Cognition in Schizophrenia, Symbol Coding (BACS SC), Category Fluency Test, Continuous Performance Test-Identical Pairs version (CPT-IP), Wechsler Memory Scale, Third Edition, Spatial Span Test (WMS-III SS), Brief Visuospatial Memory Test, Revised Edition (BVMT-R), and Neuropsychological Assessment Battery: Mazes Test (NAB Mazes). These tests encompass various cognitive domains such as processing speed, attention, verbal and visual learning, reasoning, problem-solving, and working memory. Test-retest reliability in a prior Chinese sample ranged from 0.73 to 0.94 (35).

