### Anesthesia

The MST/ECT procedure will be conducted under general anesthesia, which will include intravenous administration of etomidate (0.21–0.3 mg/kg) and propofol (1.82–2.44 mg/kg). Intravenous succinylcholine (1 mg/kg) will be administered as a muscle relaxant, while intravenous atropine (0.5 mg) will be administered to reduce airway secretions.

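### On-treatment assessments, including Day 30, are made 3 hours after an anaesthetised seizure session, so Day 30 and biomarker changes may mix acute recovery with the effect of the course; the Week 12 primary changes are not directly affected

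*Protocol article*

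**What the plan says.** Clinical measures sets the blinded clinical ratings, including HDRS-24, at time points "including baseline, post-session 3, 6, 9, and 12 (3 hours after each session", and then at the 4-, 8- and 12-week follow-up visits. Cognitive assessments ties the HVLT-R and the rest of the battery to the same schedule: "the timing of the cognitive assessments will coincide with the time points of clinical evaluations". Study summary does likewise for electrophysiology: "EEG and ECG recordings will be obtained at baseline, post-session 3, 6, 9, 12 (3 hours after each session), and at the 12-week follow-up". The Figure 1 legend agrees: "Clinical/cognitive assessments and EEG/ECG measurements are performed after every 3 sessions (end of each phase".

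Table 1 puts sessions 3, 6, 9 and 12 on Days 3, 9, 18 and 30. Day 30 is thus both a treatment day and an assessment day. Day 0 and Week 12 carry no study session.

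The Anesthesia section gives one regimen for both arms (etomidate, propofol, succinylcholine), and "intravenous atropine (0.5 mg) will be administered to reduce airway secretions". On recovery, the section on comparative side effects says that "patients receiving ECT experienced greater confusion or disorientation, and took significantly longer to regain orientation compared to MST". It gives no duration.

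Both primary outcomes (HDRS-24 and HVLT-R total recall) are changes from baseline to Week 12. The model described under Data entry and analyses looks for "significant interactions between time (baseline, Day 30, and Week 12) and condition (ECT and MST".

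**The concern.** The time factor compares values taken under different conditions. Baseline and Week 12 are free of same-day treatment. Day 30 comes 3 hours after general anaesthesia and an induced seizure. By the protocol's own account recovery from the procedure is slower after ECT. If any of that difference remains at 3 hours, it enters the Day 30 HVLT-R and possibly the HDRS-24, and cannot be separated from the effect of the twelve-session course.

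The main stake is the HVLT-R. The trial hopes to conclude that MST preserves verbal memory better than ECT. An interaction over three time points can reach significance on Day 30 alone, and could then be read as support for that conclusion even though the arms do not differ at Week 12.

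For EEG and HRV the problem is change from baseline. Every on-treatment recording follows same-day anaesthetic and atropine exposure that the baseline recording lacks. Changes in these measures are listed as secondary outcomes, and their correlation with treatment outcome is to be explored. The earlier on-treatment HDRS-24 ratings also matter somewhat, because remission before the eighth treatment counts towards completer status.

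**Working it through.** **Which values are taken 3 hours after a session**

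| Model level | Study session that day | Assessment |
|---|---|---|
| Baseline (Day 0) | none | before treatment starts |
| Day 30 | session 12 | 3 hours after the session |
| Week 12 | none | follow-up visit |

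One of the two post-baseline levels is a post-session value.

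**The plan's own figure.** The Figure 2 legend gives N = 166 for a within-between interaction with f = 0.1, 2 groups, 6 measurements and correlation 0.5.
- λ = f² × N × m / (1 − ρ) = 0.01 × 166 × 6 / 0.5 = 19.92.
- df = 5 and (166 − 2) × 5 = 820; critical F = 2.225; power = 0.950.
- 166 / 0.8 = 207.5, so 208 after 20% dropout, against 210 planned (7 × 30).

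The figure reproduces and does not depend on when in the day patients are assessed.

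**What a Day 30-only gap does to the interaction test**

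Inputs:
- Patients per arm: 105 × 0.8 = 84 (Study summary; Sample size estimation).
- Correlation 0.5, taken from the sample size calculation, with equal variances of 1 SD² at each time.
- True arm difference: d SD at Day 30, zero at baseline and Week 12. The value of d is an assumption; the documents give none.

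Changes from baseline to Day 30 and to Week 12 each have variance 2(1 − 0.5) = 1 and covariance 1 − 0.5 = 0.5. The arm difference in these two changes therefore has covariance matrix

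V = (2/84) × [[1, 0.5], [0.5, 1]].

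The inverse of the bracketed matrix has 1/0.75 = 4/3 in its first diagonal position. With mean vector (d, 0), the noncentrality is

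λ = d² × (84/2) × (4/3) = 56d².

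The 2-df chi-square test at 0.05 has critical value 5.99.

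| Assumed Day 30 gap (SD) | λ = 56d² | Chance of a significant interaction |
|---|---|---|
| 0 | 0 | 5% |
| 0.1 | 0.56 | 9% |
| 0.2 | 2.24 | 25% |
| 0.3 | 5.04 | 51% |
| 0.4 | 8.96 | 77% |

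An F test with 2 and 332 df agrees to within half a percentage point. Under the same assumptions, a direct test of the Week 12 change rejects at its nominal 5% whatever d is, because neither baseline nor Week 12 carries the gap.

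**Room in the schedule.** The day after each assessed session is Day 4, 10, 19 or 31. In Table 1 the next sessions are on Days 5, 12 and 22, and none follows Day 30. Next-day assessment leaves the treatment schedule unchanged.

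**The case against.** The strongest reply has five parts.

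1. *The primary endpoints are at Week 12, away from any session.* This stands. The primary changes do not carry an acute effect from a study session.

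2. *Nothing shows that the arm difference lasts 3 hours, and the wait may be meant to allow recovery.* The first half stands: the documents neither show persistence nor rule it out. A reader might infer that the protocol says post-ictal and drug effects last longer after ECT. It does not. It speaks only of confusion and reorientation, and the anaesthetic regimen is the same in both arms. Nor does it follow that a 3-hour HVLT-R measures only recovery; at most it mixes recovery with the effect of the course.

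3. *The percentages would follow from any Day 30 difference, including a real end-of-course deficit that resolves by Week 12.* This also stands. Next-day testing removes the same-day component but does not make a three-level interaction a test of lasting memory. That is why the fix has a second part.

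4. *EEG and HRV analyses are exploratory, and the drugs are common to both arms.* This limits the point. No between-arm bias from the drugs is shown, but common exposure does not protect change from baseline.

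5. *Raters are blinded.* A reader might infer that allocation is easiest to guess at 3 hours, or that the outcome raters also conduct the afternoon side-effect interview. The documents state neither: they describe blinded raters and cognitive assessors, and the Discussion mentions third-party evaluators. The point does not rest on unblinding, and no change to who conducts the interview is asked for.

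**Conclusion.** The concern holds as a weakness in assessment timing; the protocol does not contradict itself here. Day 30, the other on-treatment values and the EEG/HRV changes may carry an acute same-day effect of unknown size. For HVLT-R and HDRS-24 that effect could differ by arm, given the protocol's own account of slower reorientation after ECT. For EEG and HRV the drug exposure is common to both arms and bears on change from baseline.

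The consequence for inference lies in the interaction test: significance in about 5% of trials with no gap, rising to about 77% at an assumed 0.4 SD, with the arms equal at Week 12 throughout. These figures rest on 84 analysed per arm, correlation 0.5, equal variances and a gap confined to Day 30. They show sensitivity to such a gap; they are not evidence that one exists. The sample size is unaffected. The change is worth making because it is cheap.

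**What to change.** 1. For patients not yet assessed, move the clinical, cognitive, EEG and ECG assessments that follow sessions 3, 6, 9 and 12 to the next day: Days 4, 10, 19 and 31.
2. Record the date and time of each assessment relative to the last session. Account for timing in the analysis of patients already assessed at 3 hours.
3. State that any conclusion of better-preserved verbal memory rests on the between-arm contrast in HVLT-R change at Week 12, not on the three-level interaction. The planned model can supply this contrast.

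The cost is a protocol amendment and up to four return visits for any outpatients (the document does not say whether participants are inpatients). There will also be mixed timing within the Day 30 level, because the trial began in December 2024; recording the timing makes this visible but does not remove it. The third step needs no new data and is worth taking even if the timing cannot be changed.
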